### Statistical analysis

Statistical analysis will be performed using Statistical Package for Social Sciences version 17.0 (SPSS Inc., Chicago, IL, USA). Parametric and non-parametric tests will be used as appropriate to assess continuous variables for significant differences between groups. Changes in key outcomes (WOMAC, OKS, EQ-5D) from baseline to 3, 6 and 12 months following surgery will be analysed using analysis of variance (ANOVA) and adjusted for multiple testing to compare the two intervention arms. The data is expected to demonstrate a normal distribution and this will be assessed prior to analysis. A *p*-value of <0.05 will be defined as significant for the primary outcome and a *p*-value of <0.01 will be defined as significant for the secondary outcomes to adjust for multiple testing.

An economic evaluation will be conducted from an NHS perspective. Data collection from the study will also focus on estimating the cost of the interventions and subsequent use of services. Analyses will be carried out from an NHS perspective and will include the capture of resource use from secondary and primary/community care. All relevant costs associated with providing the interventions will be included including length of stay. All unit costs will be derived using routine data sources and study specific estimates. Costs in the follow-up period will include use of secondary care services, e.g. inpatient stays and outpatient visits, and primary/community care services, e.g. general practice visits, district nurse visits and prescription costs incurred over the follow-up period. This data will be collected using a health service utilisation patient diary. Data on use of services will be combined with appropriate unit costs to produce a cost for each trial participant. From these, a mean cost per intervention will be calculated. Health-related quality of life will be measured using EQ-5D-3L which is a very simple measure which patients complete at the start and end of treatment. It comprises five dimensions of health: mobility, ability to self-care, ability to undertake usual activities, pain and discomfort, and anxiety and depression. The cost-effectiveness analysis of the two types of surgery will be based on incremental cost of a quality-adjusted life year (QALY). QALYs will be estimated using the area under the curve approach. The results will be presented as point estimates of mean incremental costs and QALYs. The results of the analyses will include deterministic and stochastic sensitivity analysis, presented as point estimates and cost-effectiveness acceptability curves (CEACs).

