### Eligibility criteria

Participants listed for routine primary TKR for osteoarthritis under the care of the two participating surgeons at the institution will be screened for inclusion. The inclusion criteria are as follows: planned to undergo a primary TKR for end-stage osteoarthritis under the care of the two participating surgeons, age 45–85 at the time of listing for surgery, and suitable candidate for a cruciate retaining TKR (Triathlon prosthesis). The exclusion criteria are as follows: varus deformity of > 20° observed by consultant on examination, patient is unable to comply with the study protocol (incl. refusal for CT scan), female participants who is pregnant, lactating or planning pregnancy during the course of the study, requires patella resurfacing, inability to understand the patient information for the study, provide written informed consent or answer study questionnaires for cognitive or language reasons, or any other significant disease or disorder which, in the opinion of the Investigator, may either put the participants at risk because of participation in the study or influence the result of the study, or the participant’s ability to participate in the study.

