### Allocation

Patients are allocated once they have been screened and have given informed consent to participate in the trial. Subject numbers will be assigned sequentially as each subject enters the study. Participants will be randomised on a 1:1 ratio using the Sealed Envelope software (www.sealedenvelope.com) after consent and baseline data collection is complete to reduce the risks of selection bias. Randomisation will be carried out in random sized equally split blocks to allow even balancing of the groups and avoid selection potential bias. Patients will be allocated to standard treatment (manual TKR) or intervention group (robotic-arm- and sensor-assisted TKR). It will not be possible to conceal the allocation of treatment from the patient, or the clinicians. Research staff completing follow-up assessments and data analysts will be blinded to the participant’s allocation to reduce potential bias.

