### Outcome measures

The primary goal of joint replacement surgery is to restore function and reduce pain, the outcome measures have been chosen to reflect these factors. The primary outcome will be changed in functional ability measured by the WOMAC [18] questionnaire from baseline to 6 months following TKR. The WOMAC^18^ questionnaire consists of 24 self-administrated questions with pain, stiffness and function subscales. The score is validated for patients with knee OA to detect changes in functional ability.

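### The primary analysis compares changes from baseline by ANOVA with no baseline covariate: valid, but it gives up precision that baseline adjustment would recover at almost no cost

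*Protocol article*

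**What the plan says.** Under Outcome measures: "The primary outcome will be changed in functional ability measured by the WOMAC" questionnaire, from baseline to 6 months. Objectives specifies the functional component.

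Under Statistical analysis, the three key outcomes (WOMAC, OKS and EQ-5D) are handled as changes: "from baseline to 3, 6 and 12 months following surgery will be analysed using analysis of variance (ANOVA"). The one adjustment which that sentence goes on to name concerns multiplicity: "adjusted for multiple testing to compare the two intervention arms". A more general sentence adds: "Parametric and non-parametric tests will be used as appropriate to assess continuous variables for significant differences between groups". Neither sentence names a baseline covariate, and no other section does. The same section sets p<0.05 for the primary outcome and p<0.01 for secondary outcomes.

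Under Allocation, randomisation takes place "after consent and baseline data collection is complete to reduce the risks of selection bias". Every randomised patient should therefore have a baseline WOMAC score.

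The Sample size section uses a plain two-group comparison: 15 points, SD 26.5, alpha 0.05, 80% power, one-tailed, 40 per arm, raised to 90 randomised for 10% loss. It does not say whether 26.5 is the SD of the score or of its change.

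**The concern.** A change score subtracts the whole of the baseline value. The regression of follow-up on baseline normally has a slope below 1, so full subtraction over-corrects and adds baseline noise to the outcome. ANCOVA estimates the slope from the data and, in large samples, is never less precise than the change score.

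Precision matters in this trial. The Discussion concedes that a difference of 9 points may be clinically significant yet non-significant here, and that 102 patients would be needed to detect it. It says that funding and infrastructure were already in place. A more efficient analysis is one way to recover part of that shortfall without recruiting more patients.

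The method is named in the text, so this is a stated choice and not a detail left to an analysis plan.

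**Working it through.** **Inputs.** From Sample size: difference 15, SD 26.5, one-sided alpha 0.05, 40 per arm. From Discussion: difference 9, SD of change 18, 51 per arm. The baseline-to-6-month correlation r is not in the documents; 0.3 to 0.7 is assumed. Power is by the noncentral t distribution with 78 degrees of freedom. The one further degree of freedom that ANCOVA uses is ignored.

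**Step 1: the protocol's own figures.** The standard error is 26.5 × √(2/40) = 5.93, so the noncentrality is 15/5.93 = 2.53 and one-sided power is 80.6%. The smallest n reaching 80% is 40 per arm, as stated. The 51 per arm in the Discussion also reproduces with a one-sided t-test. Both figures are correct for an unadjusted comparison.

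**Step 2: variance ratio.** With a common SD s at both times:
- Var(change) = 2s²(1−r)
- Var(ANCOVA) = s²(1−r²)
- Ratio = (1−r)(1+r) / [2(1−r)] = (1+r)/2

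The ratio is 0.65, 0.75 and 0.85 at r = 0.3, 0.5 and 0.7, a saving of 35%, 25% and 15% of the sample.

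**Step 3: power with 40 per arm, one-sided 0.05, stated SD read as the SD of change.** Residual SD = SD of change × √((1+r)/2).

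| Case | Change score | ANCOVA r=0.3 | ANCOVA r=0.5 | ANCOVA r=0.7 |
|---|---|---|---|---|
| 15 points, SD 26.5: residual SD | 26.5 | 21.4 | 22.9 | 24.4 |
| 15 points: power | 80.6% | 92.9% | 89.5% | 85.9% |
| 9 points, SD 18: residual SD | 18 | 14.5 | 15.6 | 16.6 |
| 9 points: power | 71.6% | 86.5% | 82.0% | 77.6% |

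**Step 4: the other reading of 26.5.** If it is the SD of the score at one time, one-sided power (normal approximation, 40 per arm) goes from 69.0% for the change score to 84.3% for ANCOVA at r=0.3, from 81.2% to 89.9% at r=0.5, and from 94.8% to 97.1% at r=0.7.

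**Step 5: unequal SDs.** Let m be follow-up SD divided by baseline SD. The ratio becomes m²(1−r²)/(1+m²−2rm). At r=0.5 it is 0.64×0.75/(1+0.64−0.8) = 0.57 for m=0.8, and 1.44×0.75/(1+1.44−1.2) = 0.87 for m=1.2. The saving is larger when the follow-up SD is lower than baseline and smaller when it is higher.

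**Step 6: surgeon.** The documents give no surgeon effect. If surgeon explained an assumed 1%, 5% or 10% of the variance, one-sided power would move from 81.2% to 81.6%, 83.0% or 84.7% (normal approximation, 40 per arm).

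**The case against.** The strongest reply is that the planned analysis is valid and matches its sample size: on the stated one-sided basis it has 80.6% power, so nothing needs repair. That stands. The gain also depends on r and on the two SDs, none of which the documents give. At r=0.6 with a follow-up SD one third above baseline, the saving would be only about 3%. That stands too, and is why a range is shown.

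A reader might infer several stronger points that the documents do not support:
- **Baseline imbalance passes straight into the estimate.** It does not. The change score subtracts baseline, so only the over-corrected fraction (1 minus the regression slope) remains, with opposite sign, and it averages to zero over randomisation.
- **The primary test is diluted by the adjustment across visits.** The wording is loose, but the same section gives the primary outcome its own 0.05 threshold and says that the 0.01 for secondary outcomes is the multiplicity adjustment.
- **The trial is underpowered as analysed.** That follows only if the test is two-sided (70.5% at 40 per arm). Sample size plans a one-tailed test, and sidedness is a separate issue.
- **Omitting surgeon is a material flaw.** Patients are "under the care of the two participating surgeons" and Allocation mentions blocks but no surgeon stratum. A condensed article may leave stratification to the full protocol, and the likely gain is small. With 45 per arm and an even caseload, the chance difference in surgeon share has an SD of √(2×0.25/45) = 10.5 percentage points. An assumed 5-point surgeon difference would then shift the estimate by about 0.5 points, against a target of 15.

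**Conclusion.** The point holds as a loss of precision, not as an error of validity. Change-score ANOVA is a legitimate analysis, but ANCOVA on the same data would do the work of a sample larger by a factor of 2/(1+r): about 1.5 at r=0.3 and 1.2 at r=0.7, given equal SDs. In the 15-point case this adds power to a comparison that already reaches its target. In the Discussion's 9-point case, it takes power above 80% at r=0.3 and 0.5 and to 77.6% at r=0.7, so it recovers most or all of the shortfall listed there as a limitation.

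The direction of the gain is secure; its size is not, because r and the baseline and follow-up SDs are assumptions. The 15-point figures in the main table also read 26.5 as the SD of change. Baseline adjustment carries the point. Surgeon adjustment is optional.

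**What to change.** Make the primary analysis an ANCOVA of 6-month WOMAC function on arm and baseline WOMAC function, tested at the 0.05 threshold that the Statistical analysis section already sets for the primary outcome. A mixed model over 3, 6 and 12 months with the same baseline covariate, read at 6 months, would serve equally well. Use the same form for OKS and EQ-5D, each with its own baseline.

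Surgeon may be added as a second covariate for one further degree of freedom, without a claim of a particular gain. Fix the wording before the data are analysed by arm.

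The cost is analysis wording and one degree of freedom, or two with surgeon. No new data, patients or change to the allocation scheme are needed, and the stated sample size can stay as it is.

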## Methods/design

### Objectives

The primary aim is to compare change in functional ability (measured by the functional component of the Western Ontario and McMaster Universities Osteoarthritis Index (WOMAC) [18]) from baseline to 6 months (early) following TKR between the two groups. The secondary outcomes are:
To compare changes in knee function in activities of daily living (measured by the Oxford knee score (OKS) [19]) from baseline to 3, 6 and 12 monthsTo compare changes in joint awareness (measured by the Forgotten Joint Score (FJS) [20]) from baseline to 3, 6 and 12 monthsPre-operative patient expectation and fulfilment at 6 and 12 months will be assessed using the Hospital for Special Surgery Knee Replacement Expectations Questionnaire (HSS) [21, 22]To compare satisfaction using a validated outcome measure at 3, 6 and 12 months [23]To compare pain, stiffness and functional ability (measured by the WOMAC [18]) at 3, 6 and 12 monthsTo compare the health related quality of life using the Euro Qol five dimensional (EQ5D-3L) [24] at baseline and 3, 6 and 12 monthsTo compare the cost effectiveness of the two interventions from a UK NHS perspectiveTo analyse any differences in gait patterns between the two groups

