### Sample size

A power calculation was performed using the functional component of the WOMAC [18] as the primary outcome. Using the defined minimal clinically important difference in the WOMAC of 15 points [33], a standard deviation (SD) of 26.5, and an alpha 0.05 with a power of 80% to demonstrate a superior outcome in the intervention group (one tailed analysis), it was determined that 80 patients would need to be recruited (40 in each arm). Loss to follow-up data from other surgical arthroplasty studies in the institution with a similar follow-up regime were used to estimate a loss to follow-up of 10%. On this basis, 90 patients will be randomised to ensure the study achieves power.

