The final limitation was the use of the minimal clinically important difference of 15 points to power the study to the functional component of the WOMAC score. This was taken from Escoban et al. [33] whom defined the MCID to range from 15 to 22 points following TKR, and therefore, 15 points was taken as the lower limit and used to power the study. However, recently Clement et al. [34] have demonstrated the MCID may be as low as 9 points for the functional component of the WOMAC 1 year following TKR. Substituting this MCID of 15 for 9 and using a SD of 18 points (as observed by Clement et al. [34] for change in functional score) at least 102 patients would need to be recruited (51 in each treatment arm). Funding and study designed and infrastructure were all in place prior to the publication of this paper, and therefore, the study is continuing to aim to show a statistical 15 point or more difference, but it should be acknowledged a difference less than this may be non-significant but may be clinically significant if the difference is 9 points or more.

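### The protocol does not say that the mean-based ANOVA stands for the primary outcome whatever the normality check shows, so the primary test can be read as depending on the outcome data

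*Protocol article*

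**What the plan says.** Three statements in the Statistical analysis section of the protocol article bear on the primary test.

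- A general rule: "Parametric and non-parametric tests will be used as appropriate to assess continuous variables for significant differences between groups".
- A named method: changes in WOMAC, OKS and EQ-5D "will be analysed using analysis of variance (ANOVA) and adjusted for multiple testing to compare the two intervention arms".
- A preliminary check: "The data is expected to demonstrate a normal distribution and this will be assessed prior to analysis".

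The section gives no criterion for the check, no consequence if it fails, and no named non-parametric test. It does not say that the primary outcome keeps its ANOVA in any event. Under Objectives and Outcome measures, that outcome is the change in WOMAC function from baseline to 6 months.

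The Sample size section works in points: "Using the defined minimal clinically important difference in the WOMAC of 15 points", with "a standard deviation (SD) of 26.5", 80% power and a one-tailed alpha of 0.05, giving 40 per arm. The Discussion keeps that scale. It says that "the study is continuing to aim to show a statistical 15 point or more difference" and that a difference of 9 points or more may matter clinically.

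**The concern.** A normality check placed before the analysis, beside a general licence to use either family of tests, reads most naturally as the step that picks between them. Nothing exempts the primary outcome.

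Two things are at stake.

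1. **The question answered.** ANOVA compares mean change between arms, which is the quantity behind the 15-point target. A rank test asks whether values in one arm tend to exceed those in the other. The two coincide only if the arms differ by a pure shift. If the check triggers a switch, the primary p-value no longer concerns the quantity the trial was sized on and will be judged against.
2. **Discretion.** With no criterion stated, two candidate primary p-values exist, and the choice between them falls after the outcome data are in. Patients and surgeons know the allocation and the outcome is patient-reported, so this is latitude the trial does not need.

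**Working it through.** **Reproducing the plan's figure.** Inputs from Sample size: difference 15, SD 26.5, one-sided alpha 0.05, power 80%.

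- Normal approximation: n per arm = 2 × (1.645 + 0.842)² × 26.5² / 15² = 38.6, so 39.
- With the t distribution: 39.3, so 40 per arm and 80 in total, as stated.
- Two-sided, the normal approximation gives 49 per arm (98 in total), which does not match.
- Loss of 10%: 80 / 0.9 = 88.9, so 89; the plan randomises 90.
- Power at 40 per arm: 80.6% (t).

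The stated size is therefore that of a one-sided comparison of two means.

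**What a switching rule would do.** The protocol names no normality test, no rank test and no distribution, so these are assumptions: Shapiro-Wilk at 0.05 in either arm, then Mann-Whitney if it rejects and a t test (equivalent to two-group ANOVA) if not. Simulation: 40 per arm, 20,000 runs per setting, one-sided 0.05, the same shape in both arms.

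| Shape | Switches to rank test | Type I: t / rule / better of two | Power at 15 points: t / rule | t and rank test disagree at 15 points |
|---|---|---|---|---|
| Normal | 10% | 4.9 / 5.0 / 5.7% | 81 / 81% | 5% |
| Left skew (gamma, shape 4) | 82% | 5.2 / 5.4 / 6.4% | 81 / 85% | 8% |
| Strong left skew (gamma, shape 1.5) | >99% | 4.6 / 4.6 / 6.2% | 81 / 93% | 13% |
| Heavy tails (t, 4 df) | 64% | 4.8 / 4.9 / 6.4% | 82 / 89% | 10% |

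Three points follow.

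- The t test holds its size and its power in every row, so the check is not needed to protect validity at this sample size.
- A mechanical check adds almost nothing to type I error. Taking whichever test is more favourable gives 5.7–6.4%.
- The last column counts all trials, including those that would not switch. Counting only trials in which the rule's verdict differs from the t test's, two further one-sided simulations at 15 points gave 0.7–6.3% and 0.8–7.0% across normal, skewed and t(5) shapes.

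**When the arms differ in shape.** With a true mean difference of 0, one arm normal and the other a left-skewed gamma (shape 1.5), 10,000 runs, two-sided 0.05, the t test rejects 5.1% and the switching rule 7.9%. A second normal–gamma pairing gave 4.4% and 6.7%. In one assumed case with a true 15-point difference, one-sided power falls from 79% to 71% when the mean comparison gives way to the rank test. Here the two tests are answering different questions.

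**The case against.** The strongest reply is that the protocol already names the method. ANOVA is the specific instruction for WOMAC, and the parametric or non-parametric sentence is a general one about continuous variables. Checking an assumption before ANOVA is also compatible with using the check purely as a diagnostic, and fallback details commonly sit in an analysis plan that is not shown here. This stands to a degree. A reader might infer that the protocol commits to choosing the primary test after seeing the data. It does not say so; that is the natural reading of adjacent sentences, not an explicit rule. The absence of a criterion is not the defect either. The defect is that the text states a general choice and a prior check without saying that ANOVA survives them.

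A reader might also infer a materially inflated false-positive rate. The figures do not support that for a mechanical rule with equal shapes. The 5.7–6.4% belongs to picking the better p-value, which the protocol does not propose. Its Allocation section also keeps analysts blinded to allocation, which limits choosing by favoured arm but not choosing between p-values. No figure in the protocol shows that the arms would differ in shape.

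Nor is it right that a rank analysis can say nothing in points. A Hodges-Lehmann shift with its interval is in points and equals the mean difference under a pure shift. It does not do so in general, however, and the protocol does not name it. Finally, a rank test often gains power when both arms are similarly skewed or heavy-tailed, as the table shows.

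**Conclusion.** The point holds as a matter of target and pre-specification, not of type I error. The primary test can be read as data-dependent, and a switch would move the primary p-value away from the mean difference on which the trial is sized and interpreted.

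The practical effect is modest. With equal shapes, type I error under the switching rule is 4.6–5.4%, and the one-sided verdict at 15 points changes in about 0.7–7% of trials, under non-normal shapes mostly towards significance. The effect is clearer if the arms differ in shape: rejection of 6.7–7.9% at zero mean difference, or power of 71% instead of 79%, in the cases tried. All of these rest on an assumed Shapiro-Wilk rule, an assumed Mann-Whitney fallback and assumed distributions. The sample-size reproduction rests only on the protocol's own inputs.

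This merits a correction to the text. It does not undermine the design.

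**What to change.** State in the protocol or the analysis plan that the primary analysis is the between-arm difference in mean change in WOMAC function from baseline to 6 months, with a confidence interval, from one linear model, whatever the normality check shows. That model can be the ANOVA already named. Preferably it is ANCOVA with the baseline score as covariate, which targets the same difference.

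Then add:

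- Normality checks serve as diagnostics of the residuals only.
- If residuals are clearly non-normal, the same mean difference is kept and given a bootstrap or robust confidence interval.
- A rank test is reported as a sensitivity analysis.
- The same rule applies to OKS and EQ-5D.

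The cost is a few sentences, with no extra patients or data and no change to the 40 per arm or the 90 randomised. The one downside is some loss of power relative to a rank test if both arms turn out similarly skewed or heavy-tailed. In the simulations the fixed t test still kept its planned 81–82% there.

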‘Overall how satisfied are you with the results of your hip replacement surgery?’‘How satisfied are you with the results of your hip replacement surgery for improving your ability to do housework or yard work (such as cooking, cleaning, or gardening and raking leaves)?’‘How satisfied are you with the results of your hip replacement surgery for improving your ability to do recreational activities (such as taking walks, swimming, bicycling, playing golf, dancing, going out with friends)?’‘How satisfied are you with the results of your hip replacement surgery for relieving your pain?’

The response to each question will be recorded using a 4-point Likert scale: very satisfied, somewhat satisfied, somewhat dissatisfied and very dissatisfied. These questions and the 4-point Likert assessment have been validated and demonstrated to be reliable to measure satisfaction following primary hip replacement surgery [23]. Change in pain, stiffness, and functional ability from baseline to 3, 6 and 12 months following surgery will be assessed using the subscales of the WOMAC [18] questionnaire. Change in patient-reported quality of life from baseline to 3, 6 and 12 months following knee replacement surgery will be assessed using the EQ-5D-3L general health questionnaire [28] which evaluates five domains (-5D), which include mobility, self-care, usual activities, pain/discomfort and anxiety/depression. This is a two page questionnaire that consists of five dimensions, with the responses recorded at three levels (3L) of severity (no problems, some problems or extreme problems). The second page consists of a standard vertical 20cm visual analogue scale (EQ-5D VAS) which is transformed to a scale of 0 to 100 measuring current health-related quality of life. Each patient’s health state, derived from the EQ-5D, will be measured before and after their surgery to determine the change in their health gain or loss after their knee replacement surgery. The health state will then be multiplied by the time spent in that state to derive the QALYs gained or lost. The cost per QALY will then be calculated by dividing the cost of the procedure by the QALYs gained after TKR.

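### The article defines the QALY in two ways and mentions no baseline EQ-5D adjustment for either, so chance baseline imbalance would move the incremental QALYs in opposite directions

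*Protocol article*

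**What the plan says.** Two sections of the Protocol article describe how QALYs are formed.

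- **Statistical analysis (economic evaluation):** "QALYs will be estimated using the area under the curve approach". Costs are calculated per participant and then averaged by intervention. For the comparison, "The results will be presented as point estimates of mean incremental costs and QALYs". Deterministic and stochastic sensitivity analyses and acceptability curves are to follow.
- **Outcome measures:** each patient's EQ-5D health state "will be measured before and after their surgery to determine the change in their health gain or loss after their knee replacement surgery". It is then multiplied by time to give QALYs gained or lost, and "The cost per QALY will then be calculated by dividing the cost of the procedure by the QALYs gained after TKR".

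Three other statements bear on the point. The Statistical analysis section treats EQ-5D as a clinical outcome by change from baseline: "Changes in key outcomes (WOMAC, OKS, EQ-5D) from baseline to 3, 6 and 12 months following surgery will be analysed using analysis of variance". The economic text describes the EQ-5D-3L as something "patients complete at the start and end of treatment", whereas Objectives and Outcome measures place it at baseline, 3, 6 and 12 months. The Allocation section says "Randomisation will be carried out in random sized equally split blocks" and names no stratification factor. No covariate is mentioned for any outcome.

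**The concern.** Baseline utility is the first point on each patient's EQ-5D curve, and it usually also predicts the later points. If arm means of the area under the curve are compared without adjustment, an arm that happens to start healthier is credited with extra QALYs. Subtracting the whole baseline, as the change-based description implies, does not solve this. It removes more than the baseline predicts, so the arm that starts healthier is penalised. The same chance imbalance therefore pushes the two stated definitions in opposite directions.

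Cost-effectiveness is a listed objective. The incremental QALY is the denominator of the incremental cost per QALY and drives the acceptability curves. With about 40 patients per arm and no balancing on EQ-5D, some baseline difference should be expected.

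**Working it through.** **Inputs from the article.** EQ-5D-3L at 0, 3, 6 and 12 months (Objectives; Outcome measures). 40 evaluable patients per arm (Sample size). That sample size reproduces: a one-sided t-test for 15 points with SD 26.5, alpha 0.05 and 80% power needs 39.3, so 40 per arm. Then 80/0.9 = 88.9, so 89 against the 90 stated. The article gives no EQ-5D or QALY figure to reproduce.

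**Assumed inputs.** Baseline SD s0 = 0.20 to 0.30; follow-up SD s1 = 0.25; correlation between follow-ups 0.6; correlation of baseline with each follow-up rho = 0 to 0.5.

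**Step 1, trapezium weights (years).** Baseline 0.25/2 = 0.125; 3 months (0.25 + 0.25)/2 = 0.25; 6 months (0.25 + 0.50)/2 = 0.375; 12 months 0.50/2 = 0.25. They sum to 1; the follow-ups carry 0.875.

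**Step 2, slope of the area under the curve (AUC) on baseline.** b = 0.125 + 0.875 × rho × s1/s0.

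**Step 3, standard error (SE) of the baseline difference.** s0 × √(2/40) = 0.045 (s0 = 0.20) to 0.067 (s0 = 0.30).

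**Step 4, shift in the QALY difference for a one-SE imbalance.** For AUC: b × SE. For change multiplied by time, read as AUC minus baseline utility held for one year: (b − 1) × SE.

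**Step 5, precision.** The follow-up part of the AUC has variance 0.25² × (0.4 × 0.2656 + 0.6 × 0.7656) = 0.03535, where 0.2656 is the sum of squared follow-up weights and 0.7656 = 0.875². Then V(AUC) = 0.03535 + 0.125² × s0² + 2 × 0.125 × 0.875 × rho × s0 × s1. The proportional variance cut from adjustment is R² = b² × s0²/V(AUC). These are large-sample formulas and ignore the small cost of estimating one slope.

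*Example, s0 = 0.30 and rho = 0.3.* b = 0.125 + 0.875 × 0.3 × 0.25/0.30 = 0.344. Shifts: 0.344 × 0.067 = +0.023 and (0.344 − 1) × 0.067 = −0.044. V(AUC) = 0.03535 + 0.00141 + 0.00492 = 0.0417, so the SE of the difference is √(0.0417 × 2/40) = 0.046. R² = 0.344² × 0.09/0.0417 = 0.255, so the adjusted SE is 0.0457 × √0.745 = 0.039. For the change version, V = 0.03535 + 0.875² × 0.09 − 2 × 0.875 × 0.875 × 0.3 × 0.30 × 0.25 = 0.0698, so the SE is 0.059.

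| rho | s0 | b | AUC shift | Change shift | SE, AUC | SE, change | SE, adjusted | Variance cut vs AUC |
|---|---|---|---|---|---|---|---|---|
| 0 | 0.20 | 0.125 | +0.006 | −0.039 | 0.042 | 0.057 | 0.042 | 2% |
| 0 | 0.30 | 0.125 | +0.008 | −0.059 | 0.043 | 0.072 | 0.042 | 4% |
| 0.3 | 0.20 | 0.453 | +0.020 | −0.024 | 0.044 | 0.046 | 0.039 | 21% |
| 0.3 | 0.30 | 0.344 | +0.023 | −0.044 | 0.046 | 0.059 | 0.039 | 26% |
| 0.5 | 0.20 | 0.672 | +0.030 | −0.015 | 0.046 | 0.037 | 0.034 | 44% |
| 0.5 | 0.30 | 0.490 | +0.033 | −0.034 | 0.047 | 0.048 | 0.034 | 48% |

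The slope lies between 0 and 1 throughout, which is why the two shifts always have opposite signs. Neither stated definition is always the more precise, but the adjusted estimate has the smallest SE in every row, level with AUC to three decimals at rho = 0 and s0 = 0.20.

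**Sensitivity to the visit schedule.** If the start-and-end wording were literal, with readings at 0 and 12 months only, the baseline weight would be 0.5 instead of 0.125. A one-SE imbalance would then shift the AUC difference by 0.022 to 0.048.

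**The case against.** The strongest objection is that the article nowhere calls the QALY difference raw or unadjusted. A baseline-adjusted coefficient is also a point estimate of mean incremental QALYs, and the sentence about point estimates concerns presentation. The choice of covariates is commonly left to a health-economics plan, which is not shown, and this is a condensed article. That stands: silence about a covariate is not in itself a defect. What goes beyond silence is that the article states two different QALY constructs, which respond to baseline in opposite ways.

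A second objection is that all these comparisons are unbiased under randomisation, as is the change-score analysis of EQ-5D, and that ordinary sampling uncertainty already includes chance imbalance. This also stands. In the worked example the AUC shift of 0.023 is about half of the raw SE of 0.046, and the planned stochastic analysis would reflect that variation. The issue is precision, and error conditional on the imbalance observed. Blocked randomisation without stratification on EQ-5D is not a flaw.

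A third is that no expected QALY gain is given, so a change of sign cannot be shown. That is correct, and none is claimed. Nor does the article say how the 5-year, 10-year and lifetime projections are built, so no effect on them is claimed either.

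**Conclusion.** The point holds in a limited form. The article gives two definitions of the QALY that need reconciling and mentions baseline adjustment for neither. Comparing arm means is the most natural reading, because values are formed per patient and averaged by arm and no covariate appears anywhere, but it remains an inference. On that reading, a one-SE chance imbalance moves the AUC difference by about +0.006 to +0.033 QALY and the change-based difference by about −0.015 to −0.059. Adjustment would cut the AUC variance by about 2% to 48%. All of these sizes rest on the assumed SDs and correlations and on 40 patients per arm. The gain is slight if baseline and follow-up utility are nearly uncorrelated.

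A reader might infer that the plan fixes a raw difference, or that the cost-effectiveness result will be biased. The text supports neither: it does not specify the estimator, and randomisation removes systematic bias. A reader might also look for a gain in power, but the article specifies no hypothesis test on QALYs. This is an inexpensive improvement to a stated objective and does not threaten the trial's validity.

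**What to change.** Reconcile the Outcome measures and Statistical analysis sections to one definition: the 12-month area under the curve from EQ-5D-3L utility at baseline, 3, 6 and 12 months. Correct the start-and-end wording to match. Replace the ratio of procedure cost to QALYs gained with the incremental cost per QALY.

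Then state the estimator, for example: *Incremental QALYs will be estimated by regressing each participant's 12-month area-under-the-curve QALY on treatment arm and baseline EQ-5D-3L utility. The adjusted difference will be bootstrapped jointly with incremental cost and used for the incremental cost per QALY and the acceptability curves. The unadjusted difference will be shown as a sensitivity analysis.*

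The cost is a few sentences in the analysis or health-economics plan and one regression inside the resampling. Baseline EQ-5D-3L is already collected before randomisation, so no extra patients, visits or staff are needed.
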